# Antisecretory factor as add-on treatment for newly diagnosed glioblastoma, IDH wildtype: study protocol for a randomized double-blind placebo-controlled trial

**DOI:** 10.1186/s13063-025-08792-z

**Published:** 2025-03-13

**Keywords:** Glioblastoma, Glioblastoma, IDH wildtype, Newly diagnosed, Salovum, Antisecretory factor, Randomized clinical trial, Protocol

## Abstract

**Background:**

Glioblastoma, IDH wildtype is the most common primary malignant brain tumor in adults. Despite best available treatment, prognosis remains poor. Current standard therapy consists of surgical tumor removal followed by radiotherapy and chemotherapy with the alkylating agent temozolomide. Antisecretory factor (AF), an endogenous protein, may potentiate the effect of temozolomide and alleviate cerebral edema. Salovum® is an egg-yolk powder enriched for AF and is classified as a medical food in the European Union. Salovum® has shown preliminary clinical effect on glioblastoma in a recent pilot study. Here, we aim to assess if add-on Salovum® to temozolomide therapy can improve outcomes in patients with newly diagnosed glioblastoma.

**Methods:**

This is a multi-center, double-blinded, randomized, placebo-controlled phase II-III clinical trial to investigate superiority of Salovum® over placebo as add-on treatment for glioblastoma during concomitant and adjuvant temozolomide therapy. Patients with newly diagnosed glioblastoma that are planned for temozolomide treatment are screened for eligibility and randomized to receive Salovum® (*n* = 150) or placebo (*n* = 150). An interim analysis will be performed after 80 included patients to guide whether to continue or terminate. Primary endpoint is 12-month overall survival. Secondary outcome is 24-month overall survival.

**Discussion:**

This study will likely produce high-grade evidence to support or reject Salovum® as add-on treatment for glioblastoma.

**Trial registration:**

ClinicalTrials.gov NCT05669820. Registered on January 3, 2023.

**Supplementary Information:**

The online version contains supplementary material available at 10.1186/s13063-025-08792-z.

## Background and rationale

Glioblastoma is the most common malignant primary tumor of the brain. Despite our best efforts, prognosis remains dismal with a median survival of 7–18 months [1]. Current standard therapy consists of surgical resection followed by radiotherapy and chemotherapy with the alkylating agent temozolomide (TMZ) [2, 3].

Several different mechanisms are thought to contribute to the therapy resistance of glioblastoma. The infiltrative growth pattern makes surgical removal of all tumor cells impossible. Although surgical methods have been refined over the years, the challenge ahead lies not in surgical advancements, but in developing novel oncological or multimodal therapies. An issue when exploring new ways to treat glioblastoma is the heterogeneity of the disease, not only between different individuals, but also between regions within the tumor itself [4]. This intratumoral heterogeneity, which has been attributed to both the presence of cancer stem cells and dynamic epigenetic mechanisms, might explain the poor prognosis and rapid recurrence of glioblastoma; the tumor consists of different cellular populations which each might respond differently to therapy. Thus, there is no single druggable target, and the multitude of oncogenic pathways contribute to treatment resistance. The tumor microenvironment (TME) constitutes a complex array of cellular populations and tumor-supporting mechanisms. Glioma cells manipulate and recruit non-transformed cells to produce an advantageous TME for tumor growth. Innate and adaptive immune cells are modified to support tumor growth and to suppress an antitumor immune response. Crosstalk between these cell populations through complex signaling pathways contribute to tumor growth, angiogenesis, invasion, immunosurveillance escape, and therapy resistance [5].

In addition to multidrug resistance, glioblastoma, as most solid tumors, displays an elevated intratumoral interstitial fluid pressure (IFP) [6, 7]. The increased IFP disturbs blood flow within the TME, thereby inducing hypoxia as a driving force of angiogenesis and cancer progression. Elevated IFP may also provide a physical barrier for drug uptake to the tumor and by this mechanism further contribute to therapy resistance [7].

Antisecretory factor (AF) is an endogenous and essential protein with proposed antisecretory and anti-inflammatory properties [8]. There are currently two approved methods of increasing antisecretory factor levels in humans and animals: SPC-flakes (specially processed cereals) and Salovum®. SPC-flakes consist of oats subjected to malting, a hydrothermal treatment process. Consuming SPC-flakes stimulates endogenous production of AF [9]. Salovum® is a freeze-dried egg yolk powder based on eggs from hens fed with SPC-flakes and contains large amounts of AF [10]. Salovum® and SPC-flakes are classified as medical food by the European Union and can be bought without a prescription in pharmacies in Sweden. Salovum® has been used in clinical trials and case series for a variety of conditions, including diarrheal diseases [11–13], inflammatory bowel disease [9, 14, 15], Ménière’s disease [16–20], and traumatic brain injury [21, 22]. No adverse effects have been reported, even at high doses [13, 15, 23].

AF has been shown to reduce the elevated IFP in experimental models of solid tumors [24]. Ilkhanizadeh et al. demonstrated that exogenous administration of AF reduced IFP levels, increased drug uptake in the tumor, and inhibited tumor growth in glioblastoma-xenografted mice [25]. They also showed that SPC-flakes combined with TMZ successfully prevented tumor growth and increased overall survival at 120 days from 30 to 100% compared to TMZ monotherapy [25]. Our own results show that intratumoral delivery of an active AF peptide, AF-16, boosts the effect of intratumoral chemotherapy and immune reactivity in an experimental glioma model [26].

Glucocorticoids (GCs) play a major role in the clinical management of glioblastoma. In clinical practice, GCs are prescribed liberally to relieve neurological symptoms and brain edema induced by the tumor. There is, however, increasing evidence that GCs may have a negative impact on survival in glioblastoma patients [27]. Mechanistically, it has been proposed that GCs induce a gene signature in the tumor that contribute to a worse prognosis [28]. Long-term therapy with GCs is also associated with many unwanted side effects such as diabetes, myopathy, insomnia, anxiety, and infections. Salovum® has recently been shown to reduce increased intracranial pressure in two pilot studies on patients with traumatic brain injury [21, 22]. We hypothesize that Salovum®, by reducing tumoral IFP, might decrease the peritumoral edema in glioblastoma and thus alleviate the need for GCs. In addition, and importantly, AF might facilitate TMZ delivery to the tumor by the same mechanism.

We recently published a pilot study where newly diagnosed glioblastoma patients were treated with Salovum® as add-on to concomitant therapy. The safety and feasibility endpoints were met. As glioblastoma is a diagnosis with poor prognosis, and Salovum® appears to have no serious side effects and experimental data supports its use, this trial is clinically motivated.

### Objectives

This trial intends to evaluate if Salovum® as add-on to standard therapy in glioblastoma can improve survival compared to placebo egg yolk powder.

## Methods

### Trial design

This is a national investigator sponsored, prospective, multicenter, double-blinded, randomized, placebo controlled, phase II-III clinical trial with two parallel groups to assess superiority of Salovum® as add-on to standard treatment in glioblastoma. Allocation ratio is 1:1. Recruitment began in January 2024. Main study center is Skåne University Hospital, Lund, Sweden. Secondary study center is Linköping University Hospital, Linköping, Sweden.

### Trial population

Up to 300 patients with newly diagnosed glioblastoma will be enrolled. Patients with newly diagnosed glioblastoma who are discussed in the hospitals’ multidisciplinary treatment conference will be screened for inclusion. Eligible patients are informed and asked to participate prior to starting TMZ therapy, and consent is obtained by one of the investigators or the research nurses. The informed consent form includes use of participant data and biological specimens in ancillary studies. After 80 patients are included in this phase II-III trial, a formal interim analysis will be performed. The interim analysis will guide the investigators to either abandon or proceed to phase III, where an additional 220 patients will be included. If the interim implies that we proceed to phase III, an amendment to the ethical permit will be filed, see Ethics section.

### Inclusion criteria

The inclusion criteria are patients with newly diagnosed glioblastoma, IDH wildtype according to the 2021 WHO criteria; age between 18 and 75 years; tumor has been surgically resected; the multidisciplinary conference recommends temozolomide therapy with or without radiotherapy; and the patient is able to give informed consent.

### Exclusion criteria

The exclusion criteria are inability to give informed consent; egg yolk allergy; only needle biopsy and thus no tumor resection; and multidisciplinary conference recommends radiotherapy as monotherapy.

### Standard therapy

All patients will receive the current standard of care. Fractionated radiotherapy is delivered in 30 fractions at 2 Gy per fraction, 5 days a week for 6 weeks. Concomitant chemotherapy consists of TMZ at a dose of 75 mg/m^2^, administered 7 days per week from the first day of RT until the last, for a total of 40 days. After a 4-week break, patients receive adjuvant TMZ at a daily dose of 150–200 mg/m^2^ for 5 days in six cycles of 28 days. Older patients with good performance status and MGMT methylated tumors are sometimes allocated a shortened radiotherapy (40.05 Gy/15 fractions) with concomitant and adjuvant TMZ. If radiotherapy is contraindicated, monotherapy with adjuvant TMZ is prescribed. These two groups will be included as well as we hypothesize that Salovum® may potentiate TMZ efficacy.

Patients in good clinical condition are offered treatment with tumor treating fields.

### Ethics

This study was reviewed and approved by the Swedish Ethical Review Authority, no. 2022–00028-02, in accordance with the ethical standards of the Declaration of Helsinki. The ethical permit allows us to include the first 100 patients. If the interim analysis shows a positive trend, an amendment of the ethical application will be filed for ethical review of the phase III extension.

### Randomization

Patients included are allocated to Salovum® or placebo egg yolk powder at a ratio of 1:1. Permuted block randomization with blocks of 4–6 will be used and was compiled with R (https://www.R-project.org). To achieve balance between the centers, each study center has its own assigned block list. No stratification is performed. Each patient is assigned a unique consecutive study number. The study number is linked to a box with the same number that contains sachets of Salovum® or placebo egg yolk powder. Each sachet is also marked with the patient’s study number. The placebo and Salovum® powder as well as the packaging look and taste identical. Both patients and investigators are blinded. If a patient needs unblinding, a separate box containing envelopes marked with the patient study number can be accessed. The contents will reveal to which arm the patient was allocated. The investigator who is including the subject to intervention or placebo is unaware of the allocation, which can only be revealed by opening an opaque envelope marked only with the sequential patient study number. The contents of the envelope reveal the allocation.

The allocation sequence was generated by a statistician who is not involved in inclusion, data collection, or clinical evaluations.

The boxes are packed by the trial administrator.

### Enrollment

Patients are enrolled through the hospitals’ neuro-oncologic multidisciplinary conference. Formal inclusion is performed by the responsible research nurse and the clinically active investigators.

### Interventions

#### Active substance

The active substance is Salovum®, an egg yolk powder enriched for AF. It is produced by Lantmännen Functional Foods AB, Stockholm, Sweden and supplied for the trial.

#### Placebo

The placebo substance is egg yolk powder, which contains low amounts of AF. It will be made from freeze dried yolk and be identical to Salovum® in color, taste, texture, and smell.

#### Dosage and timing of intervention

The Salovum® and placebo powder is pre-packed in sachets of 11 g. The dose will be 11 g three times daily. Therapy will be initiated differently dependent on the recommended treatment regime. The following scenarios are possible:Concomitant (60 Gy/30 fractions or shortened with 40.05 Gy/15 fractions) and adjuvant therapy planned: Salovum® or placebo will be initiated 2 days prior to start of concomitant therapy and administered 3 times daily until 14 days after termination of the concomitant therapy. During adjuvant TMZ cycles, Salovum® will be administered from 2 days before, during, and 2 days after each cycle, a total of 9 days for each cycle.Adjuvant TMZ cycles as monotherapy planned: Salovum® or placebo will be administered 2 days before, during, and 2 days after each cycle, a total of 9 days for each cycle.If TMZ is discontinued due to tumor progression, Salovum is also discontinued.

#### Dispensing

Salovum® or placebo egg yolk powder is dissolved in at least 100 ml liquid (e.g., juice, lemonade, chocolate milk) of the patient’s choice and ingested orally. The mixture must not be heated as the proteins may denature.

#### Protocol adherence and monitoring

Protocol adherence will be monitored by frequent visits in the outpatient clinic during treatment (Table 1). Enrolled patients will have access to a research nurse that is involved in the research group. The investigators will have continuous communication with the study sites as well as frequent site visits. An external independent body (Clinical Studies Sweden, Forum South) will monitor the quality of the study. Participants who are in too poor clinical condition to participate in follow-up visits will be monitored for survival.

**Table 1 Tab1:**
[figure not shown]
Schedule for follow-up visits. Day 0 is first day of Salovum® therapy

^1^Screening is performed at multidisciplinary treatment conference
^2^Concomitant treatment startup visit
^3^Post concomitant radiochemotherapy
^4^Post adjuvant temozolomide cycles 3 and 6
^5^Neurological Assessment in Neuro-Oncology
^6^Montreal Cognitive Assessment
^7^European Organisation for Research and Treatment of Cancer Quality of Life Questionnaire C30 and BN20
^8^Current daily steroid dose is registered, date and reason for dose changes are noted

### Study endpoints

The primary endpoint is the effect of Salovum® compared to placebo as add-on to standard therapy on 12-month survival in patients with glioblastoma, IDH wildtype. The secondary endpoint is 24-month survival. Exploratory endpoints include 6- and 12-month progression free survival, median OS and PFS, Kaplan–Meier and hazard ratio analysis of long-term survival. Survival time is defined as time from first surgery to death. Progression free survival is defined as time from first surgery to progression confirmed by consensus at a multidisciplinary conference (time to next intervention). Analyses will be made using chi-square and relative risk calculations. The patients will be followed for up to 5 years. Additional exploratory analyses and sub-group analyses may be performed by multivariable analysis with covariates such as age, performance status, extent of resection, molecular markers, center, steroid medication, tumor treating fields, and second-line treatment that will be published separately. Plasma will be drawn for analysis of inflammatory cytokines, blood lipids, brain damage markers, tumor derived exosomes, and additional relevant molecules.

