### Interim analysis

A Data and Safety Monitoring Committee, consisting of at least one independent statistician and two independent clinicians with knowledge in the field, will perform an interim analysis after the 80th patient has been followed for 6 months. The DMC will assess the outcome based on 6-month PFS. If 6-month PFS differs more than 15% between the groups, the groups are unblinded. If placebo was superior, the study is terminated because of futility. If Salovum® is the superior group, the ethical permit will be amended to include 220 additional patients and continue to phase III. If 6-month PFS differs less than 15% between the groups, the groups are kept blinded and the ethical permit will be amended to include 220 additional patients and continue to phase III.

The 15% cutoff is based on data from the pilot study and our retrospective database. An increase in PFS from 71.4 to 87.5% (controls vs pilot group) is a difference of 18.4% or 16.1 percentage units.

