As a result of radiochemotherapy, a transient increase in contrast enhancement is often seen on post-radiation magnetic resonance imaging. This benign contrast enhancement is often indistinguishable from tumor recurrence and is referred to as pseudoprogression. To accurately determine whether tumor has recurred, one must look at the whole clinical picture. To minimize the risk of erroneously declaring tumor progression, we define progression as radiological or clinical progression that has led to a change in the treatment regimen or initiation of second-line therapy, as decided by consensus at the hospitals’ multidisciplinary neuro-oncological conference.

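### The PFS definition leaves out death, yet 6-month PFS alone decides the interim, so early deaths without confirmed progression do not count towards the only stopping branch.

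*Protocol article*

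**What the plan says.** Three sections of the protocol article bear on this.

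- **Study endpoints** defines the two time-to-event outcomes one after the other. For overall survival: "Survival time is defined as time from first surgery to death". For PFS: "Progression free survival is defined as time from first surgery to progression confirmed by consensus at a multidisciplinary conference (time to next intervention"). Death is named for the first and not for the second. The same section lists PFS as exploratory and names chi-square and relative risk as the analysis, which is a binary comparison at a fixed time.
- **Discussion** defines progression a second time: "we define progression as radiological or clinical progression that has led to a change in the treatment regimen or initiation of second-line therapy", again by conference consensus. Death is not mentioned here either.
- **Interim analysis** gives PFS its weight: "The DMC will assess the outcome based on 6-month PFS". The committee "will perform an interim analysis after the 80th patient has been followed for 6 months". The threshold reads: "If 6-month PFS differs more than 15% between the groups, the groups are unblinded". Placebo ahead by more than that ends the trial. Salovum ahead by more than that, or a smaller difference either way, leads to 220 further patients.

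No section says how a death before confirmed progression is handled.

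**The concern.** PFS normally counts the earlier of progression and death. Here the event is a conference decision tied to a change of treatment. A patient who deteriorates quickly and dies before the conference has decided anything does not meet either definition. In a binary 6-month comparison, that patient literally falls on the progression-free side.

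Such cases are realistic. Under Protocol adherence and monitoring the plan foresees patients too ill for visits: "Participants who are in too poor clinical condition to participate in follow-up visits will be monitored for survival".

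What is at stake is the interim. Only one branch stops the trial, and it requires placebo to be clearly ahead on 6-month PFS. If early deaths without confirmed progression were more frequent on the active product, the definition would hide them from the one comparison that could stop recruitment.

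**Working it through.** **1. Reproducing the plan's own figure.** Statistical power of endpoints gives 196 patients (98 + 98) for 6-month PFS of 71.4% versus 87.5%. The usual two-proportion formula, with two-sided alpha 0.05, power 0.80, pooled variance under the null and no continuity correction, is

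n = [1.960·√(2·p̄(1−p̄)) + 0.842·√(p1(1−p1) + p2(1−p2))]² / (p2−p1)², with p̄ = (0.714 + 0.875)/2 = 0.7945.

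This gives 97.7, so 98 per arm and 196 in all. The figure is right on its own inputs. The defect lies in the endpoint definition.

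**2. How many deaths by 6 months?** Inputs are the control survival rates in the same section: 67.3% at 12 months and 19% at 24 months. Fit a Weibull curve through both points, S(t) = exp[−a·(t/12)^k]:

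- a = −ln 0.673 = 0.396
- −ln 0.19 = 1.661
- k = ln(1.661/0.396)/ln 2 = 2.07
- S(6) = exp(−0.396 × 0.5^2.07) = exp(−0.094) = 0.91

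So about 9% are dead by 6 months, or 0.09 × 40 = 3.6 patients per arm. The documents do not say what share of these would have no confirmed progression.

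**3. The interim rule in patients.** The interim has 80 patients ("Allocation ratio is 1:1"), so about 40 per arm. One patient is 100/40 = 2.5 points. Fifteen points is 6 patients, so exceeding it needs a net difference of at least 7.

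**4. Equal omission.** Suppose PFS with death counted is 71.4% in both arms and 5% of each arm dies without confirmed progression. Leaving those deaths out turns both rates into 76.4%. The expected difference stays at zero, and the chance of exceeding the threshold in a given direction moves only from 5.3% to 4.3%.

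**5. Unequal omission and the stopping branch.** Assume both arms are 71.4% free of confirmed progression. Add assumed deaths without confirmed progression and compute the chance that placebo leads by more than 15 points (exact binomial, 40 per arm, observed proportions).

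| Assumed deaths, placebo vs Salovum | PFS with deaths counted | P(stop), deaths ignored | P(stop), deaths counted |
|---|---|---|---|
| 2% vs 5% | 69.4% vs 66.4% | 5.3% | 10.2% |
| 2% vs 10% | 69.4% vs 61.4% | 5.3% | 21.8% |

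With deaths ignored, the rule stops in either row only as often as chance would stop it with no difference at all.

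**6. The opposite error.** If PFS with death counted is truly 71.4% in both arms and the deaths are left out, the chance that Salovum appears ahead by more than 15 points rises from 5.3% to 8.5% (2% vs 5%) or 18.7% (2% vs 10%). This matters less, because the trial continues in that branch and in the small-difference branch alike.

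**The case against.** **It is a condensed article, and no sentence says such a patient counts as progression-free.** True. A reader might take that as the plan's stated rule, but the documents do not say it; such patients could also be censored or excluded. What stands is that the article does give a definition, twice, and omits death both times. Under any of these treatments the death is not an event.

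**The Discussion wording is broader than it looks.** A conference decision to stop temozolomide for progression is a change of regimen, so a patient too ill for further treatment can already have an event. A reader might infer that all such patients are lost; the documents do not support that. Nor does the sentence on very ill patients say they are followed for survival alone. The gap is deaths that no conference decision preceded. But the gloss in Study endpoints, next intervention, is narrower than the Discussion wording, and the two may classify the same patient differently.

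**Larger figures are tempting.** An exponential curve through the 12-month rate gives 1 − √0.673 = 18% dead by 6 months. It also implies 0.673² = 45% alive at 24 months, against the stated 19%, so it does not fit the plan. A shift in one arm's PFS level should also not be set against a cutoff on the difference between arms.

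**The clock starts at surgery.** A reader might infer bias. The start applies equally to both randomised arms and creates none between them.

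**The main endpoints are unaffected.** Overall survival at 12 and 24 months counts every death. This limits the point to the interim and the exploratory PFS analyses. Separately, the rule under Handling of missing data that excludes and replaces patients who end participation early may remove some very early deaths, which lowers the count but does not make those deaths events.

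**Conclusion.** The point holds for the definition and for its effect on the interim. As written, a death before any conference-confirmed progression is not a PFS event, and this weakens the only stopping branch against an excess of early deaths on the active product. Under assumed imbalances of 2% versus 5% and 2% versus 10%, the chance of stopping is about 5% with those deaths ignored, against about 10% and 22% with them counted.

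These figures rest on 40 patients per arm, a comparison of observed proportions, the 15% read as percentage points, and death rates the documents do not give. The 10% scenario is a marked excess: it is larger than the roughly 9% of all-cause deaths expected in controls by 6 months. If deaths without confirmed progression are balanced, the decision is hardly affected.

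One question remains open: whether the 71.4% and 87.5% planning rates count death. If they do, the 196 stands. If they do not, counting an assumed 5% of such deaths in each arm makes them 66.4% and 82.5%, and the same formula gives 230.

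**What to change.** - Define PFS as time from first surgery to conference-confirmed progression or death from any cause, whichever comes first. Use this for the interim and for the exploratory PFS analyses.
- Reconcile Study endpoints with the Discussion, so that one wording of the progression event (next intervention, or change of regimen) applies throughout.
- Confirm whether the pilot and database rates of 71.4% and 87.5%, and the 15% cutoff drawn from them, use the same definition. If not, restate them on it.
- Do this before the committee sees interim data. Recruitment began in January 2024, and a later change would look data-driven.

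The cost is wording and a check of the source rates. Survival is already followed, so no new data collection is needed. The 6-month PFS rates will be slightly lower than under the present definition.

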### Data collection

Data will be collected in an electronic case report form (eCRF) only accessible by authorized personnel through two-step verification (REDCap). At baseline assessment, demographic and tumor data is collected. Cognitive status (Montreal Cognitive Assessment, MoCA, scale); neurological symptoms (Neurologic Assessment in Neuro-Oncology, NANO, scale); quality of life (EORTC QLQ-C30 and QLQ-BN20 questionnaires); steroid dependence; and radiological status (RANO) will be assessed. Patients will be monitored in the outpatient clinic according to Table 1.

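### The 12- and 24-month survival comparisons are fixed to an unadjusted chi-square; pre-specified adjustment for centre and a few baseline factors would gain modest precision at little cost

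*Protocol article*

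**What the plan says.** The protocol article, Study endpoints, defines the primary endpoint as a binary comparison: "The primary endpoint is the effect of Salovum® compared to placebo as add-on to standard therapy on 12-month survival". It adds "The secondary endpoint is 24-month survival". One analysis is named for the endpoints: "Analyses will be made using chi-square and relative risk calculations". No covariate or stratum goes with it.

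The same section gives adjusted analysis a lower status: "Additional exploratory analyses and sub-group analyses may be performed by multivariable analysis with covariates such as age, performance status, extent of resection, molecular markers", and the list continues "center, steroid medication, tumor treating fields, and second-line treatment that will be published separately".

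On allocation, the Randomization section says: "To achieve balance between the centers, each study center has its own assigned block list. No stratification is performed". On baseline data, the Data collection section says: "At baseline assessment, demographic and tumor data is collected". It goes on to list cognition, neurological symptoms, quality of life, steroid dependence and radiological status.

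**The concern.** Separate permuted-block lists per centre amount to stratification by centre, and an analysis would normally reflect that. The investigators also name several baseline factors as relevant to survival, yet allocation is not balanced on them and the main test does not use them. Two things follow.

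- Outcome variation that baseline factors could explain stays in the error term, so the test is less precise than it could be.
- If the arms differ by chance in, say, age or extent of resection, the primary result can be challenged and the plan has no agreed reply. A model chosen after the data are seen would carry little weight.

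The listed covariates cannot serve as the adjustment set as they stand. They mix baseline factors with second-line treatment, which follows randomisation, and with steroid and tumour-treating-fields use, which can change after it.

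**Working it through.** **Inputs.** From Statistical power of endpoints: 12-month survival 67.3% versus 87.5%, alpha 0.05, power 0.80, 66 per arm. From the Abstract: 150 per arm planned. Assumed, because the protocol gives no measure of prognostic strength: R² (share of outcome variance explained at baseline) of 0.05 to 0.20. Also assumed: a smaller effect, 67.3% versus 80%.

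**Step 1: reproduce the protocol's sample size.** For a two-sided chi-square with pooled variance and no continuity correction,

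n per arm = [1.960·√(2p̄q̄) + 0.842·√(p₁q₁ + p₂q₂)]² / d²

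Here p̄ = 0.774, 2p̄q̄ = 0.3498, p₁q₁ + p₂q₂ = 0.2201 + 0.1094 = 0.3294 and d = 0.202. So n = (1.1593 + 0.4831)² / 0.0408 = 66.1, rounded up to 67 per arm, or 134 against the stated 132. At 66 per arm the power is 79.9%. The same formula gives 146 for 24-month survival and 196 for 6-month PFS, both exactly as stated. A one-sided test (104) or a continuity correction (152) does not give 132. The sizing therefore matches an unadjusted two-sided chi-square.

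**Step 2: power with adjustment.** Power = Φ{[d√n − 1.960·√(2p̄q̄)] / √(p₁q₁ + p₂q₂)}, with n replaced by n/(1 − R²). Example: 66/(1 − 0.10) = 73.3, so (0.202 × 8.563 − 1.1593)/0.5740 = 0.994 and power is 84.0%.

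| Per arm, rates | R² = 0 | 0.05 | 0.10 | 0.20 |
|---|---|---|---|---|
| 66, 67.3% v 87.5% | 79.9% | 82.0% | 84.0% | 88.0% |
| 150, 67.3% v 87.5% | 98.9% | 99.2% | 99.4% | 99.7% |
| 150, 67.3% v 80% | 70.6% | 72.8% | 75.1% | 80.0% |

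The 80% in the last row is not a protocol figure. It is close to what the protocol's 24-month rates imply under proportional hazards: ln 0.40 / ln 0.19 = 0.55, and 0.673^0.55 = 0.804.

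**Step 3: simulation (2,000 trials per power setting, Monte Carlo error about 0.9 points; 4,000 under the null).**

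- Centre alone, with an assumed log-odds difference of 0.5 and a 70:30 split: at 66 per arm, 80.5% for the chi-square and 81.0% for a Cochran-Mantel-Haenszel test by centre. At 150 per arm the two tests differ by less than that.
- Logistic model with one baseline score and centre, against the chi-square. At 66 per arm: 81% v 81% (R² about 0.05) and 85% v 81% (about 0.16). At 150 per arm with 67.3% v 80%: 74% v 73% and 78% v 70%.
- Type I error of the chi-square at 150 per arm: 4.8 to 5.0%, including settings with a centre effect.

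The simulation agrees with Step 2 in direction. At the low end of R² it shows little or no gain.

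**The case against.** The strongest reply is that nothing is broken. An unadjusted chi-square on a binary endpoint in a randomised trial is valid, it matches the sample-size calculation, and at the planned size and rates it already has 98.9% power. Covariate sets are often left to an analysis plan, which is not shown here.

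Most of this stands. It does not remove the point, because the protocol is not merely silent on adjustment: it names the unadjusted test and places the adjusted models among optional, separately published work. The 98.9% also depends on a 20-point effect taken from a pilot group compared with retrospective controls, and a smaller true effect is quite possible.

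Four stronger readings are tempting and not supported.

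- *That ignoring centre makes the test invalid.* Type I error stays at about 5%, and including centre adds 0.5 points or less. Consistency with the randomisation is the reason to include it.
- *That the trial loses much power as planned.* At the protocol's own rates and 150 per arm the loss is under 1 point.
- *That the Randomization section contradicts itself.* The two sentences stand side by side, and the natural reading is that no patient factor is used beyond the centre lists. The wording needs clarifying only.
- *That a log-rank or Cox analysis should be promoted because the chi-square discards event times.* Setting a 24-month log-rank against a 12-month chi-square mostly reflects the longer horizon, and 24-month survival is already the secondary endpoint. The protocol's own rates also do not imply proportional hazards: ln 0.875 / ln 0.673 = 0.34 at 12 months against 0.55 at 24 months. Hazard-ratio analysis is already planned as exploratory, and changing its rank is a trade-off.

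**Conclusion.** The point holds as an improvement in efficiency and credibility, not as an error in the test. The main survival comparisons do not use the centre lists or the baseline factors that the protocol itself names, and there is no pre-specified answer to chance imbalance.

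The power gain is negligible under the protocol's own assumptions at 300 patients. It is about 2 to 8 points at 132 patients, and about 2 to 9 points at 300 patients if the true 12-month difference is nearer 13 points. These figures rest on an assumed R² of 0.05 to 0.20, which the documents neither support nor exclude.

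Availability of the covariates is only partly documented. Demographic and tumour data are collected at baseline, but performance status and molecular markers are not itemised in Data collection, and the visit schedule table is not legible here.

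**What to change.** - Before any unblinding, including the one that the Interim analysis section allows when 6-month PFS differs by more than 15%, make the main analysis of 12-month survival, and of the 24-month secondary, a logistic model. Include treatment, centre and a short fixed list of baseline factors: age, performance status, extent of resection and, where recorded, MGMT status.
- Report the treatment effect as a standardised risk difference and relative risk. This keeps the relative risk that the protocol already intends.
- Keep the unadjusted chi-square as a sensitivity analysis.
- Leave second-line treatment, and steroid or tumour-treating-fields use after randomisation, out of this model.
- Reword the Randomization section to say that allocation was stratified by centre, with no further stratification.

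The cost is a little more analysis work and a rule for missing MGMT results. No extra patients are needed, and no new data if the listed factors are recorded at baseline as intended.
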